### Definition of analysis sets

At the cluster level, the ITT population includes all randomized ICUs that recruited subjects, regardless of the degree of adherence to the study interventions or achievement of the patient recruitment goal (50 patients per ICU). At the subject level, the ITT population includes all participants, regardless of protocol deviations. This includes patients who did not receive any ICU visits and family members who did not visit patients during the ICU stay, as well as patients who received visits longer than the maximum limit of visiting hours in both study periods (FFVM and RFVM).

### Statistical analyses

#### Patient flow

The flow of participants will be displayed in accordance with the Consolidated Standards of Reporting Trials (CONSORT) flow diagram (CONSORT 2010 statement: extension to cluster-randomized trials) [20]. This description will include information about eligibility criteria and follow-up losses at both cluster and subject levels.

#### Adherence to study interventions

The total length of visits per patient per day will be evaluated as the primary adherence variable to the study interventions. We will consider the length of stay of all visitors (whether family members or not) at the bedside of an enrolled patient during the ICU stay. For analytical purposes, we will not consider overlapping visiting hours in the total length of visits per patient per day (i.e., only the period in which there was at least one visitor [apart from the number of visitors] will be considered). The differences in the means of length of visits per patient per day between the FFVM and the RFVM groups will be compared using generalized estimating equations with adjustment for the cluster effect, period effect, and interaction between cluster and period. Additionally, we will describe the FFVM family members’ adherence to the website, and the healthcare professionals’ perception of effectiveness and barriers for implementation of the FFVM.

To assess the fidelity of FFVM implementation, we will perform on-site monitoring visits in all participant ICUs. During these visits, the ICU staff perception about adherence to proposed FFVM processes will be assessed by the coordinating center researchers using semi-structured interviews. During the FFVM period, each ICU will be rated from 0 to 100% (with higher percentages indicating higher levels of adherence to intended FFVM processes) in the following domains: (1) Visiting hours - adherence to visiting hours according to the study protocol; (2) Dissemination - dissemination of the FFVM to family members of ICU patients; (3) Structured meetings - frequency and quality of structured meetings; (4) Staff training - education of the ICU staff about the FFVM procedures. The total fidelity of the FFVM implementation score represents the mean of the four evaluated domains. We plan to perform sensitivity and exploratory analyses considering the effects of FFVM implementation on outcomes.

#### Baseline characteristics

The baseline characteristics of all participants will be presented by study arm in a table (see Table 2), but no formal statistical hypothesis testing will be performed to avoid unnecessary testing.

**Table 2 Tab2:** Baseline characteristics of study participants

	FFVM	RFVM
Patients		
Age, years: mean (SD)	xx.x (xx.x)	xx.x (xx.x)
Age ≥ 65 years: *n*/total *n* (%)	x/x (xx.x)	x/x (xx.x)
Female gender: *n*/total *n* (%)	x/x (xx.x)	x/x (xx.x)
Charlson comorbidity index: median (IQR)	xx.x (xx.x-xx.x)	xx.x (xx.x-xx.x)
History of dementia: *n*/total *n* (%)	x/x (xx.x)	x/x (xx.x)
Hazardous alcohol consumption:^a^ *n*/total *n* (%)	x/x (xx.x)	x/x (xx.x)
ICU admission type		
Medical: *n*/total *n* (%)	x/x (xx.x)	x/x (xx.x)
Emergency surgery: *n*/total *n* (%)	x/x (xx.x)	x/x (xx.x)
Elective surgery: *n*/total *n* (%)	x/x (xx.x)	x/x (xx.x)
PRE-DELIRIC score: mean (SD)	xx.x (xx.x)	xx.x (xx.x)
APACHE-II score:^b^ mean (SD)	xx.x (xx.x)	xx.x (xx.x)
SOFA score:^b^ mean (SD)	xx.x (xx.x)	xx.x (xx.x)
Mechanically ventilated: *n*/total *n* (%)	x/x (xx.x)	x/x (xx.x)
Use of vasopressor: *n*/total *n* (%)	x/x (xx.x)	x/x (xx.x)
Use of corticosteroids: *n*/total *n* (%)	x/x (xx.x)	x/x (xx.x)
Use of parenteral sedative:^b^ *n*/total *n* (%)	x/x (xx.x)	x/x (xx.x)
Use of benzodiazepine:^b^ *n*/total *n* (%)	x/x (xx.x)	x/x (xx.x)
Use of opioid:^b^ *n*/total *n* (%)	x/x (xx.x)	x/x (xx.x)
Indwelling central venous catheter: *n*/total *n* (%)	x/x (xx.x)	x/x (xx.x)
Urinary catheter: *n*/total *n* (%)	x/x (xx.x)	x/x (xx.x)
Family members		
Age, years: mean (SD)	xx.x (xx.x)	xx.x (xx.x)
Female gender: *n*/total *n* (%)	x/x (xx.x)	x/x (xx.x)
Years of education: mean (SD)	xx.x (xx.x)	xx.x (xx.x)
Household income, USD: median (IQR)	xx.x (xx.x-xx.x)	xx.x (xx.x-xx.x)
Unemployed: *n*/total *n* (%)	x/x (xx.x)	x/x (xx.x)
Living with care recipient: *n*/total *n* (%)	x/x (xx.x)	x/x (xx.x)
Surrogate decision maker: *n*/total *n* (%)	x/x (xx.x)	x/x(xx.x)
History of anxiety: *n*/total *n* (%)	x/x (xx.x)	x/x (xx.x)
History of depression: *n*/total *n* (%)	x/x (xx.x)	x/x (xx.x)
ICU professionals		
Age, years: mean (SD)	xx.x (xx.x)	xx.x (xx.x)
Female gender: *n*/total *n* (%)	x/x (xx.x)	x/x (xx.x)
Type of ICU professional		
Physician: *n*/total *n* (%)	x/x (xx.x)	x/x (xx.x)
Nurse: *n*/total *n* (%)	x/x (xx.x)	x/x (xx.x)
Nurse technician: *n*/total *n* (%)	x/x (xx.x)	x/x (xx.x)
Physiotherapist: *n*/total *n* (%)	x/x (xx.x)	x/x (xx.x)
Years of experience in ICU: mean (SD)	xx.x (xx.x)	xx.x (xx.x)
Hours of work per week: mean (SD)	xx.x (xx.x)	xx.x (xx.x)
Number of patients per professional		
Physician: mean (SD)	xx.x (xx.x)	xx.x (xx.x)
Nurse: mean (SD)	xx.x (xx.x)	xx.x (xx.x)
Nurse technician: mean (SD)	xx.x (xx.x)	xx.x (xx.x)
Physiotherapist: mean (SD)	xx.x (xx.x)	xx.x (xx.x)
Burnout syndrome at baseline:^c^ *n*/total *n* (%)	x/x (xx.x)	x/x (xx.x)

*APACHE-II* Acute Physiology and Chronic Health Evaluation-II, *FFVM* flexible family visitation model, *ICU* intensive care unit, *IQR* interquartile range (P25–P75), *PRE-DELIRIC* PREdiction of DELIRium in ICU patients, *RFVM* restrictive family visitation model, *SD* standard deviation, *SOFA* Sequential Organ Failure Assessment, *USD* United States dollars

^a^Alcohol consumption greater than or equal to 14 units per week for women and greater than or equal to 21 units per week for men

^b^Within the first 24 h of inclusion in the study

^c^Maslach Burnout Inventory total score > − 9

#### Inter-rater reliability of the CAM-ICU

Inter-rater reliability measures of the CAM-ICU will be performed before study initiation to evaluate the quality of assessment. In each participant ICU, we will assess the concordance and agreement in diagnostic classification between trained intensive care physicians (reference diagnosis) and local outcome evaluators.

#### Primary outcome

All the pre-specified study outcomes are described in Table 3. The primary outcome is the cumulative incidence of delirium during ICU stay determined by the CAM-ICU, which was validated for the Brazilian population of critical care patients [21]. The cumulative incidence of delirium is defined as the presence of delirium (at least one positive CAM-ICU score) during the ICU stay. The differences in the incidences of delirium between the FFVM and the RFVM groups will be compared using generalized estimating equations with adjustment for the cluster effect, period effect, and interaction between intervention and period and presented as risk ratio (RR) and 95% CI.

**Table 3 Tab3:** Study outcomes

Outcomes	FFVM	RFVM	Type of effect estimate	Effect estimate (CI)	*p* value^a^
Primary					
Cumulative incidence of delirium:^b^ *n*/total *n* (%)	x/x (xx.x)	x/x (xx.x)	RR	x.xx (x.xx-x.xx)*	x.xx
Secondary					
Patients					
Daily hazard of delirium:^b^ mean (SD)	xx.x (xx.x)	xx.x (xx.x)	HR	x.xx (x.xx-x.xx)**	x.xx
Any ICU-acquired infection:^c^ *n*/total *n* (%)	x/x (xx.x)	x/x (xx.x)	RR	x.xx (x.xx-x.xx)*	x.xx
Proportion of ventilator free-days: mean (SD)	xx.x (xx.x)	xx.x (xx.x)	MD	x.xx (x.xx-x.xx)**	x.xx
ICU length of stay: mean (SD)	xx.x (xx.x)	xx.x (xx.x)	MD	x.xx (x.xx-x.xx)**	x.xx
Hospital mortality: *n*/total *n* (%)	x/x (xx.x)	x/x (xx.x)	RR	x.xx (x.xx-x.xx)**	x.xx
Family members					
HADS anxiety score: mean (SD)	xx.x (xx.x)	xx.x (xx.x)	MD	x.xx (x.xx-x.xx)***	x.xx
HADS depression score: mean (SD)	xx.x (xx.x)	xx.x (xx.x)	MD	x.xx (x.xx-x.xx)***	x.xx
CCFNI satisfaction score: mean (SD)	xx.x (xx.x)	xx.x (xx.x)	MD	x.xx (x.xx-x.xx)***	x.xx
ICU professionals					
Burnout syndrome:^d^ *n*/total *n* (%)	x/x (xx.x)	x/x (xx.x)	PR	x.xx (x.xx-x.xx)*	x.xx
Tertiary					
Patients					
Need for antipsychotic agents: *n*/total *n* (%)	x/x (xx.x)	x/x (xx.x)	RR	x.xx (x.xx-x.xx)*	x.xx
Need for mechanical restraints: *n*/total *n* (%)	x/x (xx.x)	x/x (xx.x)	RR	x.xx (x.xx-x.xx)*	x.xx
Unplanned loss of invasive devices: *n*/total *n* (%)	x/x (xx.x)	x/x (xx.x)	RR	x.xx (x.xx-x.xx)*	x.xx
Proportion of coma-free days: mean (SD)	xx.x (xx.x)	xx. (xx.x)	MD	x.xx (x.xx-x.xx)*	x.xx
ICU-acquired pneumonia:^c^ *n*/total *n* (%)	x/x (xx.x)	x/x (xx.x)	RR	x.xx (x.xx-x.xx)*	x.xx
ICU-acquired UTI:^c^ *n*/total *n* (%)	x/x (xx.x)	x/x (xx.x)	RR	x.xx (x.xx-x.xx)*	x.xx
ICU-acquired BSI:^c^ *n*/total *n* (%)	x/x (xx.x)	x/x (xx.x)	RR	x.xx (x.xx-x.xx)*	x.xx
Family members					
Self-perception of involvement in patient care					
Score:^e^ mean (SD)	xx.x (xx.x)	xx.x (xx.x)	MD	x.xx (x.xx-x.xx)*	x.xx
ICU professionals					
Satisfaction of ICU professionals with the ICU visiting policy score:^f^ mean (SD)	xx.x (xx.x)	xx.x (xx.x)	MD	x.xx (x.xx-x.xx)*	x.xx

*BSI* bloodstream infection, *CCFNI* Critical Care Family Needs Inventory, *CI* confidence interval, *FFVM* flexible family visitation model, *HADS* Hospital Anxiety and Depression Scale, *HR* hazard ratio, *ICU* intensive care unit, *MD* mean difference, *PR* prevalence ratio, *RFVM* restrictive family visitation model, *RR* risk ratio, *SD* standard deviation, *UTI* urinary tract infection

^a^Adjusted for multiple comparisons with Bonferroni correction when appropriate

^b^According to the Confusion Assessment Method for the Intensive Care Unit (CAM-ICU) criteria

^c^According to the Centers for Disease Control and Prevention (CDC) criteria

^d^Maslach Burnout Inventory (MBI) total score > − 9

^e^The self-perception of involvement in patient care score varies from 0 (no involvement) to 27 (maximum degree of involvement)

^f^The satisfaction of ICU professionals with the ICU visiting policy score varies from 0 (unsatisfied) to 4 (very satisfied)

^*^95% confidence interval

^**^99% confidence interval

^***^98.3% confidence interval

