**Methods/design:**

The ICU Visits Study is a cluster-randomized crossover trial which compares an FFVM (12 consecutive ICU visiting hours per day) with an RFVM (< 4.5 ICU visiting hours per day) in 40 Brazilian adult ICUs. Participant ICUs are randomly assigned to either an FFVM or RFVM in a 1:1 ratio. After enrollment and follow-up of 25 patients, each ICU is crossed over to the other visitation model, until 25 more patients per site are enrolled and followed. The primary outcome is the cumulative incidence of delirium measured by the Confusion Assessment Method for the ICU. Secondary and tertiary outcomes include relevant measures of effectiveness and safety of ICU visiting policies among patients, family members, and ICU professionals. Herein, we describe all primary statistical procedures that will be used to evaluate the results and perform exploratory and sensitivity analyses of this study. This pre-specified statistical analysis plan was written and submitted without knowledge of the study data.

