## Statistical analysis plan

### Overall principles

The main analysis for each outcome will be performed at the subject level using the intention-to-treat (ITT) principle, meaning that all participants with a recorded outcome will be included in the analysis and will be analyzed according to the treatment group to which they were randomized (FFVM or RFVM), independent of actual visiting hours. Moreover, all analyses will account for the cluster-randomized crossover design to ensure correct type I error rates and confidence intervals (CIs). A significance level of 0.05, adjusted for multiple comparisons when appropriate, will be used for all statistical comparisons. Analysis will start once all data to discharge for the last included patient have been obtained, the database has been cleaned and locked, and the SAP has been submitted for publication. The R Development Core Team software will be used for analysis [18].

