#### Secondary outcomes

We will use the following statistical procedures to evaluate the study secondary outcomes:*Daily hazard of delirium*: The daily hazard of delirium will be analyzed using a joint survival model that accounts for the treatment effect (with adjustment for the cluster effect, period effect, and interaction between cluster and period) on repeated daily indicator of delirium within each patient and terminating event (death or discharge from the ICU) [22]. This outcome will be presented as hazard ratio (HR) and 95% CI.*Any ICU-acquired infections*: The differences in the cumulative incidence of any ICU-acquired infection between the FFVM and RFVM groups will be compared using generalized estimating equations with adjustment for the cluster effect, period effect, and interaction between intervention and period. This outcome will be presented as RR and 95% CI.*Ventilator-free days*: The number of ventilator-free days will be evaluated using the 7-day time horizon. Ventilator-free days will be set to 0 for patients who have died. The differences in the mean ventilator-free days between the FFVM and RFVM groups will be compared using generalized estimating equations with adjustment for the cluster effect, period effect, and interaction between intervention and period. This outcome will be presented as mean difference (MD) and 95% CI.*ICU length of stay*: The differences in the mean ICU length of stay between the FFVM and RFVM groups will be compared using generalized estimating equations with adjustment for the cluster effect, period effect, and interaction between intervention and period. This outcome will be presented as MD and 95% CI.*Hospital mortality*: The differences in hospital mortality rates between the FFVM and RFVM groups will be compared using generalized estimating equations with adjustment for the cluster effect, period effect, and interaction between intervention and period. This outcome will be presented as RR and 95% CI.*Symptoms of anxiety and depression among family members*: The differences in the mean HADS scores for anxiety and depression between the FFVM and RFVM groups will be compared using generalized estimating equations with adjustment for the cluster effect, period effect, and interaction between intervention and period. These outcomes will be presented as MD and 95% CI.*Satisfaction among family members*: The differences in the mean CCFNI satisfaction scores between the FFVM and RFVM groups will be compared using generalized estimating equations with adjustment for the cluster effect, period effect, and interaction between intervention and period. This outcome will be presented as MD and 95% CI.*Prevalence of burnout among the ICU professionals*: Burnout is defined as a cumulative MBI score greater than − 9. The differences in the prevalence of burnout between the FFVM and RFVM groups will be compared using generalized estimating equations with adjustment for the cluster effect and baseline MBI total scores. This outcome will be presented as prevalence ratio and 95% CI.

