#### Tertiary outcomes

We will use the following statistical procedures to evaluate the study tertiary outcomes:*Need for antipsychotic agents*: The differences in the cumulative incidence of need for antipsychotic agents during ICU stay between the FFVM and RFVM groups will be compared using generalized estimating equations with adjustment for the cluster effect, period effect, and interaction between intervention and period. This outcome will be presented as RR and 95% CI.*Need for mechanical restraints*: The differences in the cumulative incidence of need for mechanical restraints during ICU stay between the FFVM and RFVM groups will be compared using generalized estimating equations with adjustment for the cluster effect, period effect, and interaction between intervention and period. This outcome will be presented as RR and 95% CI.*Unplanned loss of invasive devices*: The differences in the cumulative incidence of any unplanned loss of invasive devices (venous catheter, enteral tube, or urinary catheter) during the ICU stay between the FFVM and RFVM groups will be compared using generalized estimating equations with adjustment for the cluster effect, period effect, and interaction between intervention and period. This outcome will be presented as RR and 95% CI.*Coma-free days at day 7*: The number of coma-free days will be evaluated using the 7-day time horizon. Coma-free days will be set to 0 for patients who have died. The differences in the mean proportion of days free of coma (RASS [23] – 4 or − 5) between the FFVM and RFVM groups will be compared using generalized estimating equations with adjustment for the cluster effect, period effect, and interaction between intervention and period. This outcome will be presented as MD and 95% CI.*ICU-acquired pneumonia*: The differences in the cumulative incidence of ICU-acquired pneumonia between the FFVM and RFVM groups will be compared using generalized estimating equations with adjustment for the cluster effect, period effect, and interaction between intervention and period. This outcome will be presented as RR and 95% CI.*ICU-acquired urinary tract infection*: The differences in the cumulative incidence of urinary tract infection between the FFVM and RFVM groups will be compared using generalized estimating equations with adjustment for the cluster effect, period effect, and interaction between intervention and period. This outcome will be presented as RR and 95% CI.*ICU-acquired bloodstream infection*: The differences in the cumulative incidence of bloodstream infection between the FFVM and RFVM groups will be compared using generalized estimating equations with adjustment for the cluster effect, period effect, and interaction between intervention and period. This outcome will be presented as RR and 95% CI.*Self-perception of involvement in patient care among the family members*: The self-perception of involvement in patient care will be evaluated using a score developed for the present study, which is composed of 9 questions related to the self-perception of involvement of the family member in the care of the patient in the following domains: (1) re-orientation activities, (2) pain control, (3) mobilization, (4) feeding, (5) hygiene, (6) emotional support, (7) helping patients to interpret ICU staff orientations, (8) helping the ICU professionals to understand patient needs, and (9) helping to create a patient-friendly environment in the patient room. The score of each question ranges from 0 (never involved in the activity) to 3 (very frequently involved in the activity). The total score, which varies from 0 (no involvement) to 27 (maximum degree of involvement), will be obtained by the sum of the scores of each question. The differences in the mean total scores of self-perception of involvement in patient care between the FFVM and RFVM groups will be compared using generalized estimating equations with adjustment for the cluster effect, period effect, and interaction between intervention and period. This outcome will be presented as MD and 95% CI.*Satisfaction among ICU professionals*: The satisfaction of ICU professionals will be evaluated through the score of the following question: Are you satisfied with the current visiting policy of your ICU? The responses to this 5-option Likert scale question may be one of the following: 0 - unsatisfied, 1- somewhat dissatisfied, 2 - indifferent, 3 - somewhat satisfied, 4 - very satisfied. The differences in the mean score values between the FFVM and RFVM groups will be compared using generalized estimating equations with adjustment for the cluster effect. This outcome will be presented as MD and 95% CI.

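### The primary model includes an intervention-by-period interaction but reports one RR without saying which contrast it is; the same wording governs 15 other outcomes

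*SAP article*

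**What the plan says.** The Primary outcome section compares delirium incidence by generalized estimating equations (GEE) with "adjustment for the cluster effect, period effect, and interaction between intervention and period and presented as risk ratio (RR) and 95% CI". Table 3 has one FFVM column, one RFVM column and one effect estimate per outcome. Nowhere does the article give the coding, a reference phase, or a rule for combining the two phases.

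The same three-part adjustment (cluster, period, intervention by period) applies to 16 of the 19 Table 3 outcomes: the primary, seven secondary (any infection, ventilator-free days, ICU stay, hospital mortality, HADS anxiety, HADS depression, CCFNI satisfaction) and eight tertiary (seven patient outcomes and family self-perceived involvement).

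The other models differ:
- Daily hazard of delirium (Secondary outcomes): "with adjustment for the cluster effect, period effect, and interaction between cluster and period".
- Visit length (Adherence to study interventions): "adjustment for the cluster effect, period effect, and interaction between cluster and period".
- Burnout: "generalized estimating equations with adjustment for the cluster effect and baseline MBI total scores".
- Professional satisfaction (Tertiary outcomes): the cluster effect only.

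Overall principles names R as the software, includes everyone with a recorded outcome under the allocated model, and promises that every analysis will respect the cluster crossover.

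**The concern.** A two-period, two-sequence crossover gains its precision because each ICU serves as its own control. In this design the intervention-by-period term is the sequence, or carry-over, contrast, and it is estimated between ICUs. Once it is in the model, the intervention coefficient is no longer a single crossover effect. Its meaning depends on how intervention and period are coded.

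Two things are at stake. First, the primary RR could be a phase-1, a phase-2 or an averaged effect, with very different precision, and the choice would remain open until analysis. An analysis plan published before database lock exists to close such choices. Second, delirium incidence and daily delirium hazard are modelled with different interaction terms and no stated reason.

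**Working it through.** The SAP article gives no power calculation, event rate or intracluster correlation (it refers to a published protocol), so there is no planned figure to reproduce. All correlations, event rates and effect sizes below are assumptions.

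**Inputs from the article.** C = 40 ICUs, 1:1 allocation to sequence, m = 25 patients per ICU per phase (40 × 2 × 25 = 2000), significance level 0.05 (taken as two-sided, in line with the 95% CIs).

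**Step 1: what the interaction is.** Let s = 1 if the ICU starts with FFVM, p = 0 or 1 for phase 1 or 2, and t = 1 under FFVM. Then t = s + p − 2sp, and it follows that t·p = (t + p − s)/2. Put this into b0 + b1·t + b2·p + g·t·p:
- the sequence term s has coefficient −g/2, so the interaction is a sequence effect;
- b1 alone is the phase-1 effect, and b1 + g is the phase-2 effect;
- b1 + g/2 is the average over the two phases.

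**Step 2: fixed ICU effects.** With ICU indicators, s is already in their span, so t·p adds nothing. A numerical check gives 43 columns and rank 42, so the interaction could not be estimated. Cluster by period taken as fixed effects has its own problem: the 80 ICU-phase cells absorb the intervention, which is constant within each cell (rank 80 with or without it).

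**Step 3: variance.** Let rho be the within-period and eta the between-period correlation, V = s2[1 + (m − 1)rho]/m and c = s2·eta, where s2 is the outcome variance.
- Crossover effect: 2(V − c)/C.
- Phase-1-only effect: 4V/C.
- Ratio: 2 / (1 − m·eta / [1 + (m − 1)rho]), which is at least 2 for any eta ≥ 0.

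| rho / eta (assumed) | Calculation | Variance ratio | SE ratio |
|---|---|---|---|
| 0 / 0 | 2/(1 − 0) | 2.0 | 1.4 |
| 0.029 / 0.014 | 2/(1 − 0.350/1.696) | 2.5 | 1.6 |
| 0.046 / 0.039 | 2/(1 − 0.975/2.104) | 3.7 | 1.9 |
| 0.089 / 0.075 | 2/(1 − 1.875/3.136) | 5.0 | 2.2 |

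Over a wider grid, the ratio is 2.2–2.5 at rho 0.01, 2.8–4.6 at rho 0.05 and 3.2–7.6 at rho 0.10 (eta from half of rho to all of it).

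**Step 4: power illustration.** Assume risks 0.25 and 0.19, rho 0.05, eta 0.04. Then s2 = 0.22 × 0.78 = 0.1716, V = 0.1716 × 2.2/25 = 0.01510 and c = 0.00686.
- Crossover: variance 2 × 0.00824/40 = 0.000412, SE 0.0203, power 84%.
- Phase 1 only: variance 4 × 0.01510/40 = 0.00151, SE 0.0389, power 34%.

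**Step 5: simulation.** 300 trials were fitted by log-link Poisson GEE with exchangeable correlation and robust SE. Assumptions: control risk about 20%, true RR 0.80, and log-scale SDs of 0.35 between ICUs and 0.17 between phases within an ICU.

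| Estimate reported | SD of log RR | Power |
|---|---|---|
| Intervention + period | 0.0901 | 69.0% |
| Interaction model, 0/1 coding, main effect | 0.1894 | 30.7% |
| Phase-1 data alone | 0.1894 | 30.7% |
| Interaction model, centred coding (average over phases) | 0.0905 | 69.3% |

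The second and third rows agree to about 1e-15 in every trial. The first and fourth are not identical on the log scale (largest difference 0.037 in log RR), but they have the same precision for practical purposes.

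**The case against.** The strongest reply is that the plan never says it will report the 0/1-coded main effect. Table 3 is not split by phase, all participants with an outcome are to be included, and the crossover is to be respected throughout. An average over the two phases fits all three statements better than a phase-1 comparison does, and Step 5 shows that averaging costs almost nothing. This stands. A reader might infer that the RR is a phase-1, between-ICU comparison, that most of the design's precision is lost, and that a real effect would probably be missed. The article does not support that inference, because it names no coding, reference phase or coefficient.

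It also stands that the non-estimable case arises only if the cluster effect means fixed ICU indicators. In GEE, clustering is ordinarily handled through the working correlation and robust variance.

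The reply does not remove the problem. An article may leave detail to a fuller document, but here the term is written out, it makes a single RR undefined without a stated contrast, and the interaction named changes between analyses. In R, the default route gives the reading that fits the rest of the plan least well.

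**Conclusion.** The point holds as a defect of definition. The primary model and 15 other outcome models include a term that leaves the single reported RR or mean difference dependent on an unstated contrast, and two analyses name a different interaction without explanation.

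The size depends on the reading. Under 0/1 coding with phase 1 as reference, the variance is at least doubled, and is about 2.5 to 5 times at the three non-zero correlation pairs assumed in the first table. Averaged over both phases, the loss is negligible. The power figures (84% against 34%; 69% against 31%) apply only under 0/1 coding and rest on assumed event rates, correlations and effect sizes. They illustrate the exposure and do not predict the trial's power.

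**What to change.** 1. For every crossover outcome, take the effect from intervention + period with ICU as the clustering unit, allowing for stronger correlation within an ICU-phase than between phases. Alternatively, keep the interaction and state that the reported RR or mean difference is the contrast averaged over the two phases.
2. Report intervention by period only as a separately labelled carry-over or consistency check that does not alter the primary estimate.
3. Reconcile the interaction wording in Adherence to study interventions, Primary outcome, Secondary outcomes and Tertiary outcomes. Where cluster by period is meant, describe it as a correlation or random term, since as fixed effects it would absorb the intervention.

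The cost is a few sentences in the plan. No data, sample size or visit schedule changes, and Step 5 shows no meaningful loss of precision. The change should be made before the outcome data are analysed.
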